**10. Study subjects**

| 10.1 | Inclusion criteria: |
| --- | --- |
| Patients with previously untreated Stages III and IVA (AJCC 6th Edition) of locally advanced NPC, and histologically confirmed NPC by biopsy, no evidence of distant metastasis, Karnofsky performance status≥70, and good bone marrow, liver and kidney function (white blood cell count ≥ 4.0×109/L, platelets ≥ 100×109/L, albumin ≥30 g/L, creatinine ≤100μmol/L). Ages eligible for study: 18 yeas to 70 years. Patients those with a prior (within 5 years) or synchronous malignancy were excluded. |
| 10.2 | Exclusion criteria: |
| There was evidence of distant metastases, previous malignancy or other concomitant malignant disease, pregnant or lactating, nasopharyngeal radiotherapy history, patients withdrew during treatment or doctor and other factors caused by violation of the study protocol. |
| 10.3 | Sample-size and rationale for calculation: |
| Sample-size= 90 ﹡  Based on the following rationale: To detect 3-year local progression-free survival (LPF） with a two-sided 5% significance level and a power of 80%, a sample size of 30 patients per group was necessary, given an anticipated dropout rate of 10%. |
| 10.4 | Number of subjects to be recruited locally in relation to this application: |
| n= 90 ﹡in applying site. |
| 10.5 | How will subjects to be identified and recruited? |
| We will publish the recruitment information of clinical trials on the website of Xuzhou Medical College Hospital (***http://www.jsxyfy.com/***). According to the specific inclusion criteria and exclusion criteria rigorous screening patients. |

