**PART Ⅱ: STUDY DETAILS**

**9.** Scientific basis

| 9.1 | Background, current evidence and key references: | | |
| --- | --- | --- | --- |
|  | Nasopharyngeal carcinoma (NPC) differs from other head and neck malignancies in terms of its epidemiology, pathology, and treatment outcomes. It is endemic in China and is one of the major public health problems. Concurrent radiotherapy and chemotherapy is the primary treatment for patients with NPC. In recent years, with the development and application of comprehensive treatment and Intensity Modulated Radiation Therapy (IMRT) technology, the overall prognosis of nasopharyngeal carcinoma has been significantly improved, 5-year survival rate was 74.5% , 3 -year local control rate was 90%[2]. Despite such aggressive treatment, many patients with locally advanced NPC still develop locally recurrent disease [3].Since local control is directly related to patient’s morbidity and mortality in NPC, there is a strong requirement to develop a method for improving current treatments’ efficacy.  One strategy to improve local control is escalating the dose of radiotherapy. This is because local control has been shown to be directly related to the radiotherapy dose . Several techniques, including brachytherapy , stereotactic radiosurgery , and dose-painting intensity modulated radiotherapy (IMRT) , have been used to increase radiotherapy dose. However, due to the large number of critical anatomic structures near the nasopharynx, dose-escalation in NPC can also lead to increased toxicities . One of the more effective techniques is the simultaneous modulated accelerated radiation therapy (SMART) IMRT technique [10]. It delivers both accelerated radiotherapy and hypofractionated radiotherapy to the GTV. The main challenge for these treatments is to identify the appropriate tumor volume that could be received the high-dose radiotherapy. Conventional dose-escalation is conducted via using computed tomography (CT) to identify the gross tumor volume (GTV). However, recent progress in the field of ﬂuorine-18-ﬂuorode-oxyglucose positron emission tomography/computed tomography (18F-FDG-PET/CT)-adjuvant treatment planning allows more accurate tumor volume delineation ]. Thus, we hypothesize that of 18F-FDG-PET/CT-adjuvant treatment planning can improve dose-escalation radiotherapy for NPC, which in turn can improve therapeutic efficacy as well as reducing toxicity.  To identify this hypothesis, we compared the efficacy and toxicity of three treatments, including conventional chemoradiotherapy, CT-guided dose-escalation chemoradiotherapy and PET/CT guided dose-escalation chemoradiotherapy, in patients with locally advanced NPC via a randomized clinical trial in our department. PET-CT fusion may have significant impact on staging and radiotherapy treatment delineation in NPC. PET/CT-guided dose escalation radiotherapy appears to be well-tolerated. The SMART-IMRT technique to enhance BED of GTV, combined with concurrent chemotherapy, is completely feasible for local advanced NPC.  [1] Wei WI, Sham JS. Nasopharyngeal carcinoma. Lancet. Jun 11-17 2005;365(9476):2 041-2054.  [2] Lu H, Peng L, Yuan X, Hao Y, et al.Concurrent chemoradiotherapy in locally advanced nasopharyngeal carcinoma: a treatment paradigm also applicable to patients in Southeast Asia. Cancer Treat Rev. 2009, 35 (4):345-353.  [3] Wee J, Tan EH, Tai BC, et al. Randomized trial of radiotherapy versus concurrent chemoradiotherapy followed by adjuvant chemotherapy in patients with American Joint Committee on Cancer/International Union against cancer stage III and IV nasopharyngeal cancer of the endemic variety. J Clin Oncol. 2005;23(27):6730-6738.  [4] Marks JE, Bedwinek JM, Lee F, Purdy JA, Perez CA. Dose-response analysis for nasopharyngeal carcinoma: an historical perspective. Cancer. Sep 15 1982;50(6):1042-1050.  [5] Teo PM, Leung SF, Tung SY, et al. Dose-response relationship of nasopharyngeal carcinoma above conventional tumoricidal level: a study by the Hong Kong nasopharyngeal carcinoma study group (HKNPCSG). Radiotherapy and oncology : journal of the European Society for Therapeutic Radiology and Oncology. Apr 2006;79(1):27-33.  [6] Teo PM, Leung SF, Lee WY, Zee B. Intracavitary brachytherapy significantly enhances local control of early T-stage nasopharyngeal carcinoma: the existence of a dose-tumor-control relationship above conventional tumoricidal dose. International journal of radiation oncology, biology, physics. Jan 15 2000;46(2):445-458.  [7] Hara W, Loo BW, Jr., Goffinet DR, et al. Excellent local control with stereotactic radiotherapy boost after external beam radiotherapy in patients with nasopharyngeal carcinoma. International journal of radiation oncology, biology, physics. Jun 1 2008;71(2):393-400.  [8] Lin S, Pan J, Han L, et al. Nasopharyngeal carcinoma treated with reduced-volume intensity-modulated radiation therapy: report on the 3-year outcome of a prospective series. Int J Radiat Oncol Biol Phys. 2009; 75(4):1071-8.  [9] Ashamalla H, Guirgius A, Bieniek E, et al. The impact of positron emission tomography/computed tomography in edge delineation of gross tumor volume for head and neck cancers [J]. Int J Radiat Oncol Biol Phy, 2007, 68 (2):388-395.  [10] Butler EB, Teh BS, Grant WH, 3rd, et al. Smart (simultaneous modulated accelerated radiation therapy) boost: a new accelerated fractionation schedule for the treatment of head and neck cancer with intensity modulated radiotherapy. International journal of radiation oncology, biology, physics. Aug 1 1999;45(1):21-32.  [11] Madani I, Duthoy W, Derie C, et al. Positron emission tomography-guided, focal-dose escalation using intensity-modulated radiotherapy for head and neck cancer. International journal of radiation oncology, biology, physics. May 1 2007;68(1):126-135.  . | | |

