**12. Study Design and Methodology**

| 12.1 | Study design: | | Prospective ﹡; and Randomized controlled trial ﹡ | | | | | | | |
| --- | --- | --- | --- | --- | --- | --- | --- | --- | --- | --- |
|  | If others, specify: | |  | | | | | | | |
| 12.1.1 | Methods of assignment: | | | Randomization | | | | | | |
| 12.1.2 | Control: | | | Concurrent control (cohort) | | | | | | |
| 12.1.3 | Degree of masking: | | | Single-blinded | | | | | | |
| 12.1.4 | Group assignment: | | | Parallel | | | | | | |
| 12.1.5 | Phase of study: | | | Phase Ⅱ | | | | | | |
| **For PhaseⅠStudy, please complete the “Supplementary Information Sheet for PhaseⅠStudy ”.** | | | | | | | | | | |
| 12.2 | Disease group (*choose the most appropriate one*) | | | | | ENT system | | | | |
| 12.2.1 | Key conditions under study *(e.g. asthma; DM etc)* | | | | | Nasopharyngeal carcinoma; SMART-IMRT; PET-CT; chemoradiotherapy | | | | |
| 12.3 | Study article (Please put “NA” on the field of “Generic name” if nor applicable) | | | | | | | | | |
| Article | Type﹡ | Generic name | | | Duration of exposure | | Dosage | Route of administration | | Was it produced under GMP? |
| 1 | Radiotherapy | SMART-IMRT;PET/CT | | | 7 Week(s) | | 77Gy | Others | | N/A |
| 2 | Radiotherapy | SMART-IMRT; CT | | | 7 Week(s) | | 70Gy | Others | | N/A |
|  |  |  | | |  | |  |  | |  |
|  |  |  | | |  | |  |  | |  |
| Control | Radiotherapy | IMRT; CT | | | 7 Week(s) | | 70Gy | Others | | N/A |
|  | | | | | | | | | | |
| 12.4 | Will an application of clinical trial certificate be made? | | | | | Yes | | | | |
| 12.5 | Has a PhaseⅠstudy been done? | | | | | Yes (for all study articles) | | | | |
| 12.6 | Number of extra visits / admissions on top of usual care: | | | | | | | | | |
| 10-20 patients in each group. | | | | | | | | | |
| 12.7 | Will any of the study interventions / procedures be performed by persons other than the investigators, and if so by whom and where? | | | | | | | | | |
| Block randomisation was by a computer generated random number list prepared by an investigator with no clinical involvement in the trial. We stratified by admission for an oncology related procedure. After the research nurse had obtained the patient’s consent, she telephoned a contact who was independent of the recruitment process for allocation consignment. | | | | | | | | | |
| 12.8 | Will biological samples or date be stored for future use? | | | | | | | | NO | |

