**15. Anticipated Benefits to Study Subjects**

| PET-CT fusion may have significant impact on staging and radiotherapy treatment delineation in NPC. PET/CT-guided dose escalation radiotherapy appears to be well-tolerated. The SMART-IMRT technique to enhance BED of GTV, combined with concurrent chemotherapy, is completely feasible for local advanced NPC. |
| --- |

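### Section 10.2 lists withdrawal during treatment and protocol violation as exclusion criteria, which permits removal of randomised patients and exposes the arm comparisons to bias

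*Protocol*

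**What the plan says.** Section 10.2 of the protocol puts "patients withdrew during treatment or doctor and other factors caused by violation of the study protocol" in the same list as baseline conditions such as distant metastases, pregnancy and earlier nasopharyngeal radiotherapy. Section 10.5 says that the inclusion and exclusion criteria are used to screen patients.

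Other parts of the protocol fix the order of events and the context:

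- Allocation (12.7): "After the research nurse had obtained the patient’s consent, she telephoned a contact who was independent of the recruitment process for allocation consignment". Section 12.3 gives every arm seven weeks of radiotherapy.
- Design (9.1): "we compared the efficacy and toxicity of three treatments, including conventional chemoradiotherapy, CT-guided dose-escalation chemoradiotherapy and PET/CT guided dose-escalation chemoradiotherapy". Section 12.3 lists 77 Gy for the PET/CT arm and 70 Gy for each of the other two.
- Masking (12.1.3): "Single-blinded", without saying who is masked.
- Sample size (10.3): 30 per group, "with a two-sided 5% significance level and a power of 80" per cent, "given an anticipated dropout rate of 10" per cent.
- Analysis (13): events are measured from randomisation. No analysis population is named, and nothing says that patients who meet the clause in 10.2 are kept.

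**The concern.** An exclusion criterion should be decidable before allocation. Withdrawal during treatment is not, and neither is a violation that arises in treatment. The clause can therefore only act on patients who already have an arm.

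Removal is unlikely to be unrelated to outcome. Patients may stop because of toxicity, early progression or deterioration. The background section says that "dose-escalation in NPC can also lead to increased toxicities", so stopping could plausibly differ between arms. The clause also covers violations caused by the doctor. Since the protocol does not say who is masked, a clinician who knows the arm might influence who is counted.

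The randomised comparison of the primary outcome (3-year LPF) and of the secondary outcomes (DFS, OS, short-term and long-term toxicity) is at stake. Tolerability is the most exposed, because it is the stated hypothesis in 9.3 and patients who could not tolerate treatment are the ones who could be dropped.

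**Working it through.** **1. Can the clause act before randomisation?** Consent comes first, then the telephone call for allocation (12.7), then seven weeks of treatment (12.3). Withdrawal during treatment falls after allocation, so the clause cannot do the screening work that 10.5 gives to the criteria.

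**2. The plan's own figure.** Section 10.3 states 30 per group with 10% dropout. 27 / (1 − 0.10) = 30, and 30 × 0.10 = 3. So 30 per group is consistent with 27 analysable patients and three lost per arm. The 27 itself cannot be reproduced, because 10.3 gives no control rate, target rate or hazard ratio.

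**3. Illustration for LPF.** The rates here are assumptions and do not come from the protocol. Let p be the true 3-year LPF, d the share of an arm removed, and q the LPF among those removed. The rate in the retained patients is

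(p − d × q) / (1 − d).

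Take p = 0.80 in both arms, so that there is no true effect.

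- 10% removed from one arm, none from the other, q = 0.50: (0.80 − 0.05) / 0.90 = 83.3%, a spurious difference of 3.3 points.
- The same with q = 0.30: (0.80 − 0.03) / 0.90 = 85.6%, a difference of 5.6 points.
- 15% against 5%, q = 0.50: 0.725 / 0.85 = 85.3% against 0.775 / 0.95 = 81.6%, a difference of 3.7 points.
- 15% against 5%, q = 0.30: 0.755 / 0.85 = 88.8% against 0.785 / 0.95 = 82.6%, a difference of 6.2 points.
- 10% from each arm with the same q: difference 0, but both arms read 83.3% (q = 0.50) or 85.6% (q = 0.30) instead of 80%.
- Any removal with q = p: no distortion.

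**4. Extreme case.** Three of 30 are removed from one arm, all three had failed, and the retained rate is 90%. Then 0.90 × 27 = 24.3 (an expected count), 24.3 / 27 = 90% and 24.3 / 30 = 81%. The overstatement is 9 points. This bounds the case of three removals with 90% among the retained; larger removals could do more.

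**5. Illustration for toxicity.** Section 14.7 gives grade 3 mucositis of 28.6% to 31.8%. Suppose that this is the rate in 27 retained patients and that the three removed all had it.

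- (0.286 × 27 + 3) / 30 = 10.72 / 30 = 35.7%, against 28.6% reported.
- (0.318 × 27 + 3) / 30 = 11.59 / 30 = 38.6%, against 31.8% reported.

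The arm's rate would be understated by about 7 points. The figure reaches 10 points (3/30 against 0/27) only if no retained patient has the event.

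**The case against.** The strongest reply is that 10.2 is an eligibility list and does not say that data are dropped from any analysis. The wording is garbled and may be a misplaced list of discontinuation reasons. Section 10.3 expects some dropout, section 13 counts events from randomisation, and analysis populations are often left to the analysis plan, which is not at hand here. This stands in part: the text permits removal but does not prove that it will happen. It does not rescue the clause. A protocol that makes non-completion an exclusion criterion states a rule, and nothing in the document offsets it. An analysis plan that kept these patients would contradict it.

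Four stronger readings are tempting, and the document does not support them.

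- *Every comparison is biased.* Balanced removal of patients with the same prognosis leaves the between-arm difference intact, as step 3 shows.
- *The higher-dose arm is favoured.* Section 9.1 says that escalation can raise toxicity, but it also hypothesises that PET/CT planning lowers it. Which of the three arms would lose more patients cannot be read from the protocol.
- *The bias is about 9 points and uses up the room for improvement.* That equates the 10% dropout in 10.3 with removals under 10.2, which the protocol does not link; dropout could be loss to follow-up over three years. It also treats the 90% local control in 9.1, a background figure, as this trial's control rate.
- *The metastasis criterion would remove patients from the PET/CT arm alone, after its planning scan.* Section 12.3 names PET/CT for one arm only. The protocol does not say when the scan is done relative to randomisation, nor that a scan finding removes a patient already allocated.

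**Conclusion.** The point holds. Section 10.2, as written, permits randomised patients to be removed for events that occur after allocation and may be linked to treatment. This exposes LPF, DFS, OS and toxicity to bias, with the tolerability hypothesis most directly at risk.

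The size is illustrative only. Removing 10% from one arm alone gives a spurious LPF difference of about 3.3 to 5.6 points, which rests on an assumed true LPF of 80% and on 50% to 30% among those removed. The direction is unknown, since it depends on how removals differ by arm and on the prognosis of those removed. That the clause is there and can only act after allocation is certain; how much bias would follow is not.

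**What to change.** Delete the clause from 10.2. Record withdrawal from treatment and protocol violation as treatment discontinuations or protocol deviations, and state that neither removes a randomised patient.

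Analyse all randomised patients in the arm assigned. Continue outcome follow-up after treatment stops, unless the patient withdraws consent to follow-up; in that case censor at the last contact. The text should separate stopping treatment from withdrawing consent, because the present wording does not. Analyse toxicity in all patients who received any radiotherapy. An analysis of completers may be kept as a sensitivity analysis.

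The cost is a short protocol change and continued follow-up of a few patients per arm: about three if removals ran at the 10% that 10.3 allows for dropout.

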| 9.2 | Aim of study: | | |
|  | This pilot trial is designed to determine whether PET/CT-guided radiotherapy dose escalation can improve local control while minimizing toxicity for the treatment of locally advanced nasopharyngeal carcinoma. | | |
| 9.3 | Hypothesis (e.g. *Compared to x control, y intervention leads to a greater rate of z outcome.*) | | |
| PET/CT-guided dose escalation radiotherapy is well-tolerated for patients with locally advanced NPC as compared to conventional chemoradiotherapy. | | |
| 9.4 | Primary outcome(s) | Outcome measure(s) | Time-point |
| Local progression-free survival (LPF） | 3-year |
|  |  |
| 9.5 | Secondary outcome(s) | Disease-free survival (DFS) | 3-year |
| Overall survival (OS) | 3-year |
| Short term toxicity | 3-month |
| Long term toxicity | 3-year |
|  |  |
| 9.6 | In what way will the research contribute to knowledge or healthcare development? | | |
|  | The project findings will be published in the form of paper, to be published 2-4 papers. The results of this study will be used on the clinical. | | |

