**13. Methods of Statistical Analysis**

| All events were measured from the date of randomization. OS was defined as the time from the date of radiotherapy to death or the latest date known to be alive. Durations were calculated from the end of treatment. The Kaplan-Meier method was used to calculate the actuarial rates of local control, DFS and OS. The χ2 test was used to compare incidence rates and categorical variables and Student’s t-test was used to compare the means of continuous variables, designated to be significant at p<0.05. |
| --- |

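### Item 10.2 lists events that can only happen after randomisation as exclusion criteria; followed as written, it removes randomised patients because of what happened to them on treatment

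*Protocol*

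**What the plan says.** Item 10.2 gives the exclusion criteria. Most are facts that can be established at screening: distant metastases, other malignancy, pregnancy or lactation, earlier radiotherapy to the nasopharynx. The last entry is different: "patients withdrew during treatment or doctor and other factors caused by violation of the study protocol".

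The other relevant statements in the protocol are these.

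- **Design (12.1):** "Randomized controlled trial", with parallel groups.
- **Allocation (12.7):** once the research nurse had consent, "she telephoned a contact who was independent of the recruitment process for allocation consignment".
- **Treatment (12.3):** 7 weeks in each of the three arms.
- **Hypothesis (9.3):** "PET/CT-guided dose escalation radiotherapy is well-tolerated for patients with locally advanced NPC as compared to conventional chemoradiotherapy".
- **Outcomes (9.4, 9.5):** LPF at 3 years is primary. DFS, OS, and short-term and long-term toxicity are secondary.
- **Sample size (10.3):** 30 per group, "given an anticipated dropout rate of 10" per cent.
- **Analysis (13):** "All events were measured from the date of randomization". Nothing here or elsewhere in the protocol cancels the clause in 10.2.

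**The concern.** An eligibility criterion should rest on what is known before allocation. Withdrawal during treatment cannot be known then, and neither can a departure from protocol that occurs in the course of treatment. As an exclusion, the clause can only act on patients already randomised, and it selects them by what happened on treatment.

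That undoes what randomisation provides. The patients left in each arm are those who completed treatment without a violation, and the reasons for not completing may differ between arms.

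This matters more here than in many trials. The hypothesis is about tolerability, and stopping treatment is one way in which poor tolerance shows itself. Section 9.1 says that escalating the dose near critical structures may increase toxicity. If toxicity leads to withdrawal and withdrawal leads to exclusion, toxicity is understated in the arm where this happens more often. The primary outcome is exposed too, because patients who did not complete treatment may have a different risk of local failure from those who did. If follow-up also stops at exclusion, their outcomes cannot be recovered later.

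**Working it through.** **Step 1. Order of events.** Consent, then telephone allocation (12.7), then 7 weeks of treatment (12.3). Withdrawal during treatment falls in the third stage, after randomisation. The clause is therefore a post-randomisation exclusion, whatever its intent.

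**Step 2. The plan's own figure.** 10.3 gives 30 per group with 10% dropout. The dropout step is consistent with 27 evaluable patients per group: 27 / (1 − 0.10) = 30. The 27 itself cannot be reproduced, because 10.3 states no control rate, target rate or hazard ratio; that is a separate matter and does not affect this point. The 10% is used below only to set a scale: 0.10 × 30 = 3 patients per arm.

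**Step 3. Effect on LPF in one arm.** Let F be the number of local failures among 30, k the number excluded, and m the number of failures among those excluded. As a simplification, 3-year LPF is treated as a proportion without censoring.

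Apparent LPF = (30 − F − (k − m)) / (30 − k)

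Assume a true LPF of 90% (F = 3; section 9.1 quotes 90% for 3-year local control as background, not as a design assumption) and k = 3:

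| Failures among the 3 excluded (m) | Apparent LPF |
|---|---|
| 0 | 24/27 = 88.9% |
| 1 | 25/27 = 92.6% |
| 2 | 26/27 = 96.3% |
| 3 | 27/27 = 100% |

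The shift runs from −1.1 to +10 percentage points with no change in what the treatment does. With a true LPF of 80% (F = 6) the range is 21/27 = 77.8% to 24/27 = 88.9%.

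**Step 4. Effect on toxicity in one arm.** Item 14.7 quotes grade 3 mucositis of 28.6% to 31.8%. Take 9/30 = 30% as a round figure in that range, and suppose that all k excluded patients had grade 3 toxicity:

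Apparent rate = (9 − k) / (30 − k)

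| Grade 3 patients excluded (k) | Apparent rate |
|---|---|
| 1 | 8/29 = 27.6% |
| 2 | 7/28 = 25.0% |
| 3 | 6/27 = 22.2% |

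If instead 3 patients were excluded and none had grade 3 toxicity, the rate would rise to 9/27 = 33.3%. The understatement therefore depends on withdrawals being related to toxicity.

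**The case against.** The strongest reply is that the clause is garbled and sits in an eligibility field. Item 10.5 says the criteria are used to screen patients. The clause may be a misplaced rule on discontinuation. It does not say in terms that such patients leave the analysis, that follow-up stops, or that toxicity already recorded is discarded. Section 13 measures events from randomisation, which suits an as-randomised analysis, and the definition of analysis populations may be left to a statistical analysis plan that is not at hand.

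Part of this stands. Removal from the analysis is the natural reading of an exclusion that can only apply after allocation, but it is a reading. The silence of section 13 on analysis populations is not a fault in itself. The point rests on what 10.2 states: a later plan that analysed all randomised patients would have to contradict 10.2 as written.

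Three stronger readings are tempting, and the protocol does not support them.

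- A reader might infer that the patients removed are those who could not tolerate escalation. The protocol gives no reasons for withdrawal. Violations due to the doctor or other factors need not be related to toxicity or to arm. Section 9.1 makes the mechanism plausible and no more.
- A reader might infer that the bias must favour the PET/CT arm on local control. Step 3 shows that it can run either way.
- A reader might take the 10% allowance in 10.3 as confirming that these patients are dropped. An ordinary dropout allowance does not show that.

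**Conclusion.** The clause is wrong as written and should be corrected. It makes post-randomisation events grounds for exclusion in a randomised comparison, and no other statement in the protocol cancels it. If it is followed, the comparison is no longer as randomised; that conclusion needs no assumption about why patients withdraw.

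The direction and size of the bias do need assumptions. Toxicity would probably be understated in any arm with more toxicity-driven withdrawals. LPF could be biased up or down. With 3 of 30 excluded from an arm, a true LPF of 90% could appear as 88.9% to 100%, and a 30% grade 3 rate could appear as low as 22.2%. These are bounds on what three exclusions can do in an arm of this size, not forecasts. They assume that exclusions reach the protocol's dropout rate, and the lowest toxicity figure assumes that all three excluded patients had grade 3 toxicity. The protocol supplies no figure for a true difference in toxicity between arms, so no loss of power is claimed.

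**What to change.** 1. In 10.2, delete the clause, so that eligibility rests only on facts known before randomisation. If it was meant as a rule on discontinuation, it should be taken out of the eligibility criteria and labelled as such.
2. In section 13, state that LPF, DFS and OS are analysed in all randomised patients in the arm assigned, with follow-up continued after treatment stops.
3. In section 13, state that toxicity is reported for all patients who started radiotherapy, including those who withdrew.
4. Allow an analysis without withdrawals and violators only as a labelled sensitivity analysis, with numbers and reasons by arm.

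The 10% allowance in 10.3 can stay as it is.

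The cost is one deleted clause, a few added sentences, and continued follow-up of the patients who stop treatment, at the time points already set in 9.4 and 9.5. No extra patients are needed and no treatment changes. The small downside is that including non-adherent patients may slightly dilute the estimated effect of treatment as delivered; the sensitivity analysis addresses that question.
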